#### 3.1.2 Randomisation and Vaccine Allocation Procedure

A total of 60 volunteers will be recruited for the study and allocated to six vaccination groups at random. The aim will be to recruit all 60 volunteers before the intended start of the study. If this is not achieved we will randomise in two blocks of 30 volunteers. The randomisation procedure will be performed in the following way :

When participants are found to be eligible and have signed their informed consent they will be numbered 1 to 60 (in order of enrolment) the treatments (vaccine formulations) will be randomly assigned to 6 groups of 10 numbers through a specific randomisation computer program. These groups will be the 6 treatment groups. We will not randomise for sex and/or age.

#### 3.1.3 Blinding and Code Breaking Procedure

Vaccines will be administered in a single blind manner, i.e., only the vaccinator will know the vaccine adjuvant given to the subject. A research nurse will perform the vaccinations. Neither physicians, nor technicians will know the adjuvant.

Randomisation will be performed at EMVI. Randomisation list will be provided as scratchable lists (similar to lottery scratchboards). The randomisation lists will be made available to the Pharmacist in charge of the preparation of the vaccine and to the safety monitor in Nijmegen and one copy will be kept in the EMVI Executive Director office in Copenhagen. The original randomisation list will be kept by the statistician of the trial.

*Code-breaking :*

[figure not shown]

The code can be broken by one of the randomisation list holders or by the statistician only in case of serious adverse event needing urgent treatment depending on the vaccine and/or adjuvant the subject has received

The Safety Monitor, however, may break the code if it is absolutely necessary for the monitoring of the safety of the volunteers to unblind. This certainly applies if holding rules or stopping rules are being discussed. Please refer to section 6.2.2.

In case of pregnancy or SAE's, the safety monitor will break the code in order to inform GSK and EMVI about the adjuvant used. In this case, the investigator will remain blinded, unless unblinding is absolutely necessary.

The requirement should come from the investigator and /or the EMVI Clinical and regulatory Affairs Director after discussion with the Principal investigator, if possible.

If the code is broken it must be documented and reported. A code breaking form will allow the above users to report the code breaking request and code breaking result.

In case of significant difference in rate of severe reactions as defined in section 7.1.2, within the 3 different adjuvant groups, codes will be broken for the statistical analysis after the primary immunisation series of the 10µg dosage step, in order to decide or not the continuation of the vaccination with the higher dose.

The different vaccine formulations will be prepared in the NCMLS pharmacist under sterile conditions. Each syringe will be labelled/coded according to a randomisation document (key document). Vaccine labels will contain the code number (see section 5).

The vaccination will be carried out by a research nurse. This nurse will be the only one who knows which vaccination formulation is given to a certain volunteer. Neither volunteer nor the physicians who evaluate the reactions to the vaccinations will know the adjuvant. The physician will know the dose of AMA-1 in the vaccine formulation since this protocol dictates a step-up procedure starting with the 10 µg AMA-1 dose. The technicians who will perform the immunological assays will also be blinded to vaccine group.

## **3.2 Trial Plan**

### **3.2.1 Trial Calendar/Timelines**

Study protocol will be submitted to the Institutional Review Board of UMCN, and has to be approved before volunteers will be recruited. Written informed consent will be obtained from volunteers after free discussion with the Principal Investigator or Co-Investigator, following the procedure of Informed Consent (see Appendix 8). At least two weeks will be allowed before consent signature. Volunteers will be informed that they will not gain health benefits from this study and of the potential risks they may be exposed to.

In January 2005 we will submit the study protocol to the IRBN. We plan to start approximately June 2005 with the trial. For safety reasons we will start with the 10µgr AMA-1 formulations. Every week a group of 15 volunteers will start (see flow chart). Volunteers will be followed for one year. September 2006 the study will be finished. (see GANTT chart below)

[figure not shown]

### 3.2.2 Vaccination, Clinical Follow-up and Serology schedule

The vaccination and serology schedule is summarized in the flow chart (see page 9). Each subject will attend at 13 standardised visits at the trial centre (Inclusion visit D-28; D0; D1; D14; D28; D29; D42; D56; D112; D113; D126; D140; D365). Two doses of vaccine at 4 week-interval will be given by intra-muscular route at D0 and D28. A booster dose will be given 12 weeks after the primary series at D112.

Blood samples will be taken at ten time points at D-28; D0; D7, D28; D35, D56; D112; D119, D140, and D365. Before each vaccination and 7 and 28 days after each vaccination a venapuncture will be performed. Biological parameters are assessed at inclusion, 7 and 28 days after each vaccination and after a year. Blood for immunologic assays will be collected at inclusion, before each vaccination, 28 days after each vaccination and a year after the first immunisation. A venapuncture will be performed ten times during the course of the study. A maximum total of 40 mL blood will be taken at each blood sampling. For each subject a maximum of 400 mL blood will be taken during the whole study.

Twenty four hours, 3 days, 7 days and 14 days after each vaccination a visit is planned to monitor adverse events at D1, D3, D7, ,D14, D29, D31, D35, D42, D113, D114, D119 and D126.

[figure not shown]

### 3.2.3 Trial Centres

The study will be performed at a single centre at the University Medical Center St. Radboud, Nijmegen

[figure not shown]

### **3.2.4 Conduct of the Trial**

#### ***Interruption of the Trial***

The trial may be discontinued for the following reasons:

1. administrative reasons if new data about the investigational product resulting from this or any other trials become available,
2. and/or on advice of the sponsor,
3. and/or on advice of the investigators, and/or the IRBs/Ethics Committee(s).

If a trial is prematurely terminated or suspended, the sponsor shall promptly inform the investigators, the Regulatory Authorities and the IRB of the reason for termination or suspension (as specified by the applicable regulatory requirements).

#### ***Safety Monitor***

A safety monitor from UMC-St Radboud will be involved in the review of severe and serious adverse events and volunteer safety. He will be independent from both the investigator team and the sponsor team. His main responsibility will be the assessment of the events and recommendation on withdrawal of the subjects or a group of subjects from further vaccination. Please refer to the Safety Monitoring Plan 6.2 for more information.

### **3.3 Case Report Forms and Data Collection**

#### **3.3.1 Source Data**

All data collected by the investigator is reported in the CRF's. Therefore, the CRF is also considered source data.

Since all subjects will be healthy, there is no medical file for the trial subjects, with exception of the medical file in case of adverse events/reactions resulting in a medical consultation or an hospitalisation. In this case the medical file will be considered as the source data.

For the clinical follow-up of the vaccine injection, the diaries are considered as source data. Thus they should be kept as source document in the investigator clinical file.

#### **3.3.2 Diary**

All subjects will receive diary cards which are the source document for the follow-up surveillance during the 14 days after each injection. (see section 7.1)

Diaries will be given to each subject at time of the vaccination visit, i.e. V2, V7 and V13. The diary will contain all solicited local and systemic reactions, as standardised data, as well as open fields for unsolicited reactions/events.

Subjects will be provided with a ruler for daily measurement of the size of local reactions at vaccination sites, and with a thermometer for daily measurement of temperature. The procedures for measurement will be explained each time a diary is provided. At day 3 and 7 after each vaccination, the investigator will check that the data collection is properly done.

The diaries will be collected on the 14-day following each vaccination, i.e. V4, V7, and V11. The data collected in the diary will be reported in the case report form.

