## FLOW CHART

**Prime & Boost phase, 19 Visits, 3 Vaccinations, Randomised, Dose Escalating, 365 Days duration/subject**

| Visit Number                    | V1                                          | V2              | V3               | V4         | V5         | V6              | V7               | V8            | V9         | V10        | V11             | V12               | V13                  | V14            | V15         | V16         | V17             | V18              | V19           |
|---------------------------------|---------------------------------------------|-----------------|------------------|------------|------------|-----------------|------------------|---------------|------------|------------|-----------------|-------------------|----------------------|----------------|-------------|-------------|-----------------|------------------|---------------|
| Trial Timelines (Days,)         | D-28                                        | D0              | D1               | D3         | D7         | D14             | D28              | D29           | D31        | D35        | D42             | D56               | D112                 | D113           | D115        | D119        | D126            | D140             | D365          |
| Time Windows (Days or Hours)    |                                             | ± 7 D           | ± 6 hrs          | ± 24 hrs   | ± 24 hrs   | ± 2 D           | ± 2 D            | ± 6 hrs       | ± 24hrs    | ± 24 hrs   | ± 2 D           | ± 2 D             | ±7 D                 | ± 6 hrs        | ± 24hrs     | ± 24 hrs    | ± 2 D           | ± 2D             | ± 14 D        |
| Visit Intervals                 |                                             | V1
+4
wks | V2
+24
hrs | V2
+ 3D | V2
+ 7D | V2
+2
wks | V4
+ 2
wks | V7
+ 24hrs | V7
+ 3D | V7
+ 7D | V7
+2
wks | V11
+ 2
wks | V7
+12wks         | V13
+ 24hrs | V13
+ 3D | V13
+ 7D | V9
+2
wks | V11
+2
wks | V1
+1 year |
| Vaccination Doses               |                                             | Vac1     |                  |            |            |                 | Vac2      |               |            |            |                 |                   | Vac3          |                |             |             |                 |                  |               |

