| Termination record / interim    |                                             |                 |                  |            |            |                 |                  |               |            |            |                 | X                 |                      |                |             |             |                 | X                |               |
| Termination record / Final      |                                             |                 |                  |            |            |                 |                  |               |            |            |                 |                   |                      |                |             |             |                 |                  | X             |
| Diary card provided             |                                             | DC1             |                  |            |            |                 | DC2              |               |            |            |                 |                   | DC3                  |                |             |             |                 |                  |               |
| Diary card collected            |                                             |                 |                  |            |            | DC1             |                  |               |            |            | DC2             |                   |                      |                |             | DC3         |                 |                  |               |
| Case Report Form Sections       | CRFA                                        |                 |                  |            |            |                 | CRFB             |               |            |            |                 |                   | CRFC                 |                |             |             |                 |                  | CRFD          |

[figure not shown]

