# **7 EVALUATION CRITERIA**

## **7.1 Primary Evaluation Criterion : Safety**

### **7.1.1 Definition of the Criterion**

The safety profile will be assessed on the following criteria

- Immediate reactogenicity; defined as any systemic adverse reactions occurring within 30 minutes after each injection,
- Local and systemic reactogenicity measured from day 0 to day 14 after each dose
- Any unsolicited adverse event resulting in a visit to a physician between each injection and one month after the third dose.
- Any Serious Adverse Event (SAE) occurring from the inclusion through out the study. The relationship of the adverse event to the study vaccine will be established by the investigator, using the following definitions : related or not related.
- Biological safety, one month after each vaccination, in reference with the baseline before the first dose, by measuring the following :
  - RBC, hemoglobin, hematocrit, MCV, MCH, MCHC, platelets, WBC with differential counts
  - Potassium, sodium, ASAT, ALAT, total bilirubin, alkaline phosphatase,  $\gamma$ GT, creatinin

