### 7.1.3 Method and Timing of Measurement

#### 1. *Local reactions*

The duration of the **pain** will be measured in minutes, hours or days, and the severity scale as 1) mild: easily tolerated, does not interfere with daily life 2) moderate: discomfort that interferes with or limits usual daily activity 3) severe: disabling, inability to perform usual daily activity, including a functional limitation of the movement.

The duration of redness, swelling, and other local reaction will be measured in hours or in days.

The size of redness, swelling, will be measured in cm with a rule, the maximum length will be reported on the CRF, in mm. **Redness, or swelling**. of less than 20 mm is mild, of 20-50 mm is moderate, and of greater than 50 mm is severe

Solicited local reactions will be recorded at visits V2; V3, V4; V5, V6, V, V8, V9, V10, V11, V13, V14, V15, V16 and V17. The subjects will report daily the local reactions in their diary from day 1 to day 14 after the vaccination.

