#### 2. *Systemic reactions*

The duration in hours or in days of all systemic reaction will be monitored by the investigator, as well as the time interval of occurrence after the last vaccination.

Oral temperature will be measured with a thermometer and the intensity of **fever** will be defined as 1) mild when comprised between 37°,5°C and 38°C, 2) moderate when comprised between 38°C and 39,0°C and 3) severe when > 39,0°C.

[figure not shown]

The systemic reactions will be monitored at visits V2; V3, V4; V5, V6, V7, V8, V9, V10, V11 and V12. The subjects will report daily the systemic reactions in their diary from day 0 to day 14 after the vaccination.

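### The visit codes for collecting diaries and recording systemic reactions conflict with the protocol's own 14-day reactogenicity window, most clearly after dose 3

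*Protocol*

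**What the plan says.** The primary criterion in section 7.1.1 is "Local and systemic reactogenicity measured from day 0 to day 14 after each dose". Section 3.3.2 makes the diary "the source document for the follow-up surveillance during the 14 days after each injection".

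The visit codes that should deliver this window are given in several places:

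- **Hand-out (section 3.3.2):** "Diaries will be given to each subject at time of the vaccination visit, i.e. V2, V7 and V13".
- **Collection (section 3.3.2):** "The diaries will be collected on the 14-day following each vaccination, i.e. V4, V7, and V11".
- **Collection (flow chart, row "Diary card collected"):** diary 1 at V6, diary 2 at V11, diary 3 at V16.
- **Systemic reactions (section 7.1.3):** "The systemic reactions will be monitored at visits V2; V3, V4; V5, V6, V7, V8, V9, V10, V11 and V12".
- **Local reactions (section 7.1.3):** the visit list runs on to V17, and for the diary "The subjects will report daily the local reactions in their diary from day 1 to day 14 after the vaccination". Systemic diary entries start on day 0.

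The flow chart is headed "Prime & Boost phase, 19 Visits, 3 Vaccinations". Section 3.2.2 instead lists 13 standardised visits, and both volunteer checklists in Appendix 8 also say 13.

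**The concern.** The diary is the source record for the primary endpoint, and section 7.1.2 asks for the rate, duration and severity of reactions over 14 days. A card taken back on day 7 truncates the recorded duration of any reaction still present. It also leaves no daily entries for the second week, and does so for dose 3 only. Descriptive tables by dose would then rest on unequal windows. The safety summary in section 6.2.3 is meant to cover the 14-day period after every vaccination and would draw on the same shortened record.

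The systemic list has a similar gap. Read in the flow-chart numbering, it contains no visit after the third dose, while the local list in the same section does.

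**Working it through.** There is no sample-size formula here. The check is to map each visit code to a day and subtract the day of the dose.

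**Inputs.** Doses fall on D0, D28 and D112. In the flow chart V2 = D0, V4 = D3, V6 = D14, V7 = D28, V11 = D42, V12 = D56, V13 = D112, V14 = D113, V15 = D115, V16 = D119 and V17 = D126. The 13 visits of section 3.2.2 carry no codes. Numbering them in order gives V4 = D14, V7 = D42, V9 = D112, V11 = D126, V12 = D140 and V13 = D365.

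**Day-14 visits in the flow chart.** 0 + 14 = D14 (V6); 28 + 14 = D42 (V11); 112 + 14 = D126 (V17).

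**Section 3.3.2 collection codes.**

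| Code | Flow chart | Relative to doses | 13-visit list |
|---|---|---|---|
| V4 | D3 | dose 1 + 3 | D14 = dose 1 + 14 |
| V7 | D28 | dose 2 + 0 | D42 = dose 2 + 14 |
| V11 | D42 | dose 2 + 14; 112 − 42 = 70 days before dose 3 | D126 = dose 3 + 14 |

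The stated day-14 rule is reproduced only with the 13-visit list. The hand-out codes in the same section need the flow chart: V13 is D112 there, but D365 in the 13-visit list. No single numbering makes section 3.3.2 consistent.

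The same mixture appears elsewhere. The flow chart's interval row places V17 two weeks after V9, which works only if V9 is D112 (112 + 14 = 126). In the chart itself V9 is D31. Section 7.4.3 likewise puts the D112 sample at V9.

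**Flow-chart collection.** Diary 1 at V6 is dose 1 + 14. Diary 2 at V11 is dose 2 + 14 (42 − 28). Diary 3 at V16 is dose 3 + 7 (119 − 112). The 13-visit list has no V16, so leftover numbering cannot account for this cell.

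**Loss if V16 is followed.** Days 8 to 14 after dose 3 are lost, that is 14 − 7 = 7 of 14 diary days. If all 60 subjects receive dose 3 and return the card on D119 exactly, that is 60 × 7 = 420 of 60 × 14 = 840 dose-3 diary days. The ± 24-hour window at V16 moves collection to day 6 to 8. Section 6.2.3 counts the period as the vaccination day plus 13 further days. On that count days 8 to 13 are lost, 6 of 14.

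**Reaction visits between D112 and D126.**

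- Systemic list in section 7.1.3: none, since it ends at V12 = D56.
- Local list in section 7.1.3: V13, V14, V15, V16 and V17.
- Flow-chart solicited-events row: V14, V15, V16 and V17.

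**The case against.** The strongest reply is that the 14-day design is never in doubt. Sections 3.3.2, 6.3.2, 7.1.1, 7.1.2 and 7.1.3 all state 14 days in words, and most of the wrong codes are remnants of a 13-visit schedule. The systemic list probably has the same origin, because V12 in that schedule is D140 and V9 to V12 would cover dose 3. Section 7.1.3 also asks for daily systemic diary entries after vaccination, and the flow chart marks solicited events at V14 to V17. The post-dose-3 period is therefore not left unobserved.

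Most of this stands, and it rules out three stronger readings that a reader might infer:

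- **The first diary is taken back on day 3, losing 11 of 14 days.** The sentence naming V4 itself says day 14, section 3.3.2 makes day 3 only a check on data collection, and the flow chart collects diary 1 at V6.
- **Nothing is scheduled at V17 or after dose 3.** V17 is in the local list and the solicited-events row. It is missing only from the diary-collection codes and the systemic list.
- **Dose 3 will look falsely well tolerated and hide sensitisation.** The protocol plans only descriptive analysis by group and says nothing of sensitisation. It also reports that adult reactions to RTS,S/AS02A usually resolve within 4 days, so an effect on reaction rates is not shown.

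The reply does not explain diary 3 at V16, nor the two numberings within one section. The 13-visit count is also still in force in section 3.2.2 and Appendix 8, so staff have no authoritative scheme to fall back on.

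**Conclusion.** The operational schedule for the primary reactogenicity endpoint is wrong as written and should be corrected. The firmest element is the flow-chart cell for diary 3: followed literally, it costs the daily record for days 8 to 14 after dose 3, 7 of 14 days. That loss assumes that staff act on the cell rather than on the 14-day text. It concerns daily diary entries only, because the V17 visit can still pick up reactions, though less precisely for onset and duration.

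The V4/V7/V11 codes and the systemic list ending at V12 are numbering conflicts. They show that the codes cannot be relied on, but not that data will be lost. The day-1 start of the local diary is minor, because local reactions are also recorded at the vaccination visits V2 and V13. The documents give no onset or duration data for this vaccine, so the effect on reported rates or durations cannot be sized.

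**What to change.** 1. Use the flow chart's 19-visit numbering throughout. Correct the 13-visit statements in section 3.2.2 and in both Appendix 8 checklists, and check the codes in the flow chart's interval row and section 7.4.3 against it.
2. Set diary collection to V6, V11 and V17 in section 3.3.2, and move diary 3 from V16 to V17 in the flow chart.
3. Extend the systemic list in section 7.1.3 to the dose-3 visits through V17. Including V13 matches the local list and the 30-minute surveillance marked there. The solicited-events row leaves vaccination visits blank, so a footnote should say that day-0 reactions are recorded under immediate surveillance and the diary.
4. Start the local diary on day 0, as for systemic reactions, and state once whether the window ends on day 13 (section 6.2.3) or day 14 (section 7.1.1).

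The cost is a set of visit codes and one diary start day, best changed before diaries and case report forms are printed. No visit or blood sample is added.

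### A visit on day 12 is within its window but can take the diary back before its last one or two days are filled in, because collection is not tied to the final entry

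*Protocol*

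**What the plan says.** The primary safety criterion in section 7.1.1 includes "Local and systemic reactogenicity measured from day 0 to day 14 after each dose". Section 7.1.3 sets the diary to match. For local reactions, "The subjects will report daily the local reactions in their diary from day 1 to day 14 after the vaccination". For systemic reactions, "The subjects will report daily the systemic reactions in their diary from day 0 to day 14 after the vaccination". Section 3.3.2 gives the diary its standing: subjects receive "diary cards which are the source document for the follow-up surveillance during the 14 days after each injection".

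On collection, section 3.3.2 states: "The diaries will be collected on the 14-day following each vaccination", and gives the visits as V4, V7 and V11. In the flow chart V4 is D3, V7 is D28 and V11 is D42, so only V11 is a day-14 visit. The flow-chart row "Diary card collected" places card 1 at V6 (D14), card 2 at V11 (D42) and card 3 at V16 (D119, which is day 7 after dose 3). The flow chart gives each of the day-14 visits V6, V11 and V17 a tolerance of two days either way.

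Section 6.2.3 uses a different period for reactogenicity: the vaccination day plus the next 13 days, so day 0 to day 13. It also requires a reactogenicity summary to reach the Safety Monitor by Day 19.

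**The concern.** The diary is meant to run to day 14, but the visit at which it is handed in may properly take place on day 12 or 13. No section says that the subject keeps the card until the last day has been entered. A site that follows the flow chart could collect the card early and record no visit deviation, with the end of the primary reactogenicity record blank.

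At stake are the daily ruler and thermometer readings and daily grades on the last one or two days. The length of the self-recorded period would also differ between subjects for reasons unrelated to the vaccine. Section 7.1.2 names rate, duration and severity over the 14 days as the measured parameters. The groups have 10 subjects each and the analysis is descriptive, so uneven follow-up would pass straight into the tables.

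This is separate from the wrong visit codes. Card 2 is assigned to V11 in both places and is already exposed. If cards 1 and 3 are moved to the day-14 visits, all three sit on visits with the same tolerance.

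**Working it through.** The protocol states no figure to reproduce. The check is a count of calendar days.

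**Inputs**
- Nominal collection day: 14 (section 3.3.2).
- Visit tolerance at V6, V11 and V17: 2 days either way (flow chart).
- Last diary day: 14 (sections 7.1.1 and 7.1.3) or 13 (section 6.2.3).
- Length of record: days 0 to 14 = 15 days; local diary days 1 to 14 = 14 days; days 0 to 13 = 14 days.

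**Permitted collection days**: 14 − 2 = 12 to 14 + 2 = 16.

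**Full days lost** = max(0, last diary day − collection day).

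| Collected on day | Lost if record ends on day 14 | Lost if record ends on day 13 |
|---|---|---|
| 12 | 2 | 1 |
| 13 | 1 | 0 |
| 14 | 0 | 0 |
| 15 | 0 | 0 |
| 16 | 0 | 0 |

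**Largest loss within the window**
- Day 0 to 14: 2/15 = 13%. Local diary: 2/14 = 14%.
- Day 0 to 13: 1/14 = 7%.
- If the entry for the collection day is also unfinished at the visit, add one day: 3/15 = 20% and 3/14 = 21%, or 2/14 = 14% under day 0 to 13.

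**Share of diaries affected.** The protocol gives no attendance pattern, so the share can lie anywhere from 0% (no early visits) to 100% (all early). As an illustration only, assume that visits spread evenly over days 12 to 16:
- Day 0 to 14: 2/5 = 40% lose at least one full day; mean (2 + 1)/5 = 0.6 day.
- Day 0 to 13: 1/5 = 20% lose one day; mean 1/5 = 0.2 day.

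**What later visits can recover**
- Dose 1: the next visit is V7 (D28). The flow chart marks no solicited-event check there, but section 7.1.3 lists V7 for systemic reactions.
- Dose 2: the next visit is V12 (D56). The flow chart marks solicited events, and section 7.1.3 lists V12 for systemic reactions.
- Dose 3: the next visit is V18 (D140). Neither the flow chart nor section 7.1.3 lists it.
- In each case the next visit is nominally 28 days after the dose (28 − 0, 56 − 28, 140 − 112). That is 28 − 19 = 9 days after the Day-19 summary is due.

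**Time available for a late card.** A card collected at the latest permitted visit (day 16) leaves 19 − 16 = 3 days before Day 19. A card completed on day 14 and posted on day 15 leaves 19 − 15 = 4 days.

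**The case against.** The strongest reply is that the protocol does not authorise a 12-day diary. Section 3.3.2 names day 14 and section 7.1.3 requires daily entries to that day; the two-day tolerance belongs to the visit. This stands in part. A card taken back on day 12 respects the visit window but breaks the diary instruction. The fault is therefore that the two rules are not tied together. It is not a positive permission to stop early.

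A reader might also infer that reactions on the last days go unrecorded and that ongoing reactions have their duration cut. The documents do not support this. Section 6.3.2 requires duration and outcome for each event. Section 6.3.3 requires all adverse events within one month of each dose to be recorded, with inquiry at every visit. Sections 6.3.3 and 6.4 have unresolved events reviewed at later visits. A reaction present on day 12 therefore stays open until it ends, and a later one can be reported. What inquiry cannot recreate is the daily measurement.

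The holding rule in section 6.2.2 adds little. A card collected on day 12 cannot show more than 48 hours at Grade 3 for an onset after day 10. A card ending on day 14 has the same limit for an onset after day 12. The rule also needs 5 of 10 subjects and works from the data manager's tables.

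Finally, the wrong visit codes are the larger fault in this part of the protocol: collecting card 3 at V16 could lose a week. That is true, and the same correction should deal with both.

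**Conclusion.** The point holds as a minor conflict between stated rules. Within the visit window, a diary can be taken back with up to two full days of self-measured size, temperature and grade missing under the day 0 to 14 definition, or one under day 0 to 13. These maxima follow from the protocol's own windows and need no assumption about attendance beyond a visit on day 12. They apply now to cards 1 and 2 under the flow chart, and to card 3 only once its collection is moved to V17.

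The 40% and 20% shares must not be read as predictions. They rest on an assumed even spread of visits, and the true share is unknown. Nor is it right to say that the lost days have no route to recovery. The adverse event form applies throughout, and V7 and V12 give partial cover, although the flow chart and section 7.1.3 disagree about V7. Recovery at these visits would normally come after the Day-19 summary.

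**What to change.** 1. Reconcile the last diary day between sections 7.1.1 and 7.1.3 (day 14) and section 6.2.3 (day 13).
2. Correct the collection visits in section 3.3.2 and the flow chart so that each card is tied to the day-14 visit of its dose (V6, V11, V17).
3. Add one sentence to section 3.3.2, with a matching flow-chart note: the card is not collected before the entry for the last diary day is complete; if the visit falls earlier, the subject keeps the card and returns it by post in time for the Day-19 safety report.

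Changing the visit window to 0 to + 2 days is optional. The sentence on hand-in protects the data by itself. A narrower window would turn visits on day 12 or 13 into deviations from the flow-chart intervals that section 7.4.3 uses to define the per-protocol population.

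The cost is a few wording changes and an occasional posted card to chase. No vaccination timing or holding rule is touched.
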